### Statistical analysis

R studio Version 1.2.1335 (http://www.R-project.org) and Empower (www.empowerstats.com, X&Y solutions, Inc., Boston, MA) were utilized for statistical analysis. Categorical data are expressed as numbers and rates, while continuous data are expressed as means ± standard deviation (SD) if they are normally distributed, or median (interquartile range [IQR]) vice versa. Student’s *t* test or Mann-Whitney *U* test is used for univariate analysis of continuous data, and the *χ*^2^ test or Fisher’s exact test is used for categorical data. For primary analyses, multivariate logistic regression is adopted to calculate adjusted odds ratios (ORs) and 95% confidence interval (95% CI) for short-term outcomes. Cox proportional hazard regression analysis is used to generate adjusted hazard ratio (HR) and corresponding 95% CI for long-term outcomes. The primary and secondary end points will be analyzed in the modified intention-to-treat analysis, which includes all subjects undergo randomization and subsequent interventions. Sensitivity analyses of primary and secondary endpoints are performed in the per-protocol population, based on the treatment actually received. The noninferiority margin was set at 10 percentage points for the absolute difference between groups. If the standard of noninferiority was reached, the primary and secondary outcomes were subsequently tested for superiority (*P*<0.05). Noninferiority will be considered proven if conclusions drawn from the intention-to-treat and per protocol analyses are consistent.

Further pre-specified subgroup analyses will be carried out in the following subgroups: TASC II C-D lesions versus A-B lesions, occlusion versus stenosis. Adjustment analyses for primary and secondary endpoints were performed based on the Hochberg method [16]. Multiple imputation was used to handle missing data.

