### Follow-up and outcomes of interest

Primary outcome and secondary outcomes are set based on patient-centered outcomes. All included patients will be followed up in outpatient clinics using questionnaires at 1 month, 6 months, 12 months, 24 months, and 36 months after the initial intervention. Patients who are unable to return will be followed up on telephone. Duplex ultrasound will be tested routinely at 1, 6, 12, 24, and 36 months post-index procedure; CTA will be routinely tested at 12 and 36 months post-index procedure; and if duplex US suggests restenosis at the target lesion, a further CTA examination will be performed to assess the stenosis. If the restenosis is more than 50% and the patient’s symptoms are worse (e.g., shorter claudication distance or exacerbation of pain), reintervention will be carried out. Patients who are unable to return to clinic will be suggested to undergo computed tomography angiography (CTA) or duplex ultrasonography in local hospital. Images and medical records will be sent to investigators online. Trained outcomes assessor will collect the outcomes of interest, blinded to the intervention groups.

The timepoint for the primary outcome of this study is 12 months. Patients are defined as dropout if they meet the following criteria: (1) lost to follow-up for less than 12 months post-intervention: a subject is considered loss to follow-up if cannot be contacted via fifth attempts by telephone and WeChat message. (2) Withdrawal consent to participation of the study: all participants have the right to withdraw from the study at any time for any reason.

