#### Primary outcome

Target lesion revascularization (TLR) of the target lesion(s) assessed at 12 months after the intervention (TLR is defined as the first revascularization procedure (e.g., percutaneous transluminal angioplasty (PTA), atherectomy, and catheter-directed thrombolysis)) when the primary patency is lost.

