#### Secondary outcomes

The following secondary endpoints of this study are collected at 1, 6, 12, 24, and 36 months post-index procedure:

(1) Stent and/or surgery related mortality; (2) all-cause mortality; (3) amputation-free survival; (4) acute limb ischemia rate; (5) major adverse cardiovascular and cerebrovascular events (MACCEs); (6) target vessel revascularization (TVR) (TVR is defined as the first revascularization procedure (e.g. PTA, stenting, surgical bypass, etc.) in the target vessel(s)); (7) primary patency (the loss of primary patency is defined as target lesion(s) is determined to be > 50% stenosis or TLR/TLR needed in follow up); (8) primary assisted patency (the loss of primary assisted patency is defined as target lesion(s) is determined to be > 50% stenosis after TLR); (9) secondary patency (the loss of secondary patency is defined as target lesion(s) is determined to be > 50% stenosis after endovascular procedure or surgical bypass TVR); and (10) stent-related complication (e.g., stent kinking or fracture).

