### Sample size calculation

We calculated the sample size for this study based on the results of previous studies [4, 13]. As is reported previously in AIOD patients, the 9-month primary patency of CBE stent (BARD®LIFESTREAM™ Stent) was 89.1%, while the 9-month primary patency of the CSE stent (GORE® VIABAHN™ stent) was estimated to be 82.2% based on VIASTAR Trial [14, 15]. In the present study, we hypothesized that the primary patency of CBE stent is not inferior to that of CSE stent; the predetermined noninferiority margin on risk difference scale (δ) is set as 10% between treatment groups. The type I error rate is 0.05, the power of the test is set as 80%, and the randomization ratio is set as 1:1. After accounting for a 15% dropout rate. It was calculated that 53 lesions per group are needed for a total of 106 lesions.

In order to achieve adequate participant enrollment, we will recruit patients by putting up posters or advertising on the Internet, furthermore, we actively recruit patients from outpatient department and emergency department.

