## Discussion

The past three decades have witnessed open surgery shift to endovascular strategies as the preferred treatment for mild-to-moderate-to-severe AIOD. Endovascular therapy is increasingly preferred as the first-line treatment in most AIOD patients. Different stents have different designs (covered stents, bare metal stents, self-expanding stents and balloon-expandable stents) but which type is the best for AIOD patients has yet to be fully elucidated [17].

Previous studies have shown that covered stents can create a smooth hemodynamically favorable lumen and resist hyperplastic ingrowth through BMS interstices; in addition, covered stents can also protect against iliac artery rupture post-dilation [8, 10, 18]. Self-expandable stents have high elasticity and small radial force, which helped to prevent circumferential stress and subsequently enhanced neointimal proliferation. This may be the reason why self-expandable bare metal stents led to a decreased incidence of restenosis at 12 months compared with treatment with balloon-expandable bare metal stents [9]. However, the best choice between CBE stent and CSE stent is left to the interventionalist’s preference and lack of RCT data now, leading to there is no consensus or relevant guidelines on which stents should be used in AIOD.

The Viabahn stent and LifeStream stent represent one of the most widely used CSE and CBE stents, respectively. A previous study showed that Viabahn covered stent can be considered an acceptable patency with low complications during the long-term period in low-risk young AIOD patients [4], especially for complex aortoiliac occlusion lesions [19]. Another study indicated that the LifeStream stent provided satisfactory 9-month clinical outcomes, including a low rate of TLR for the treatment of stenotic and occlusive lesions of the iliac arteries [15]. However, there is no long-term period patency or TLR of the LifeStream stent. Furthermore, there is no cohort or RCT study to compare the efficacy or effect between Viabahn stent and LifeStream stent. The main aim of our present trial is to compare TLR of the target lesion of LifeStream stent with Viabahn at 12 months’ follow-up.

In conclusion, this trial was designed to compare the efficacy and safety of a CBE stent (BARD®LIFESTREAM™) versus a CSE stent (GORE® VIABAHN™) in AIOD patients, hoping to provide level 1 evidence for stent selection in aortoiliac occlusive lesions.

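### With about 13 to 15 expected patency losses and fewer TLRs, an ordinary adjusted odds ratio is biased and sometimes not finite; the noninferiority decision itself is not affected

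*Protocol article*

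**What the plan says.** In the protocol article, the Statistical analysis section states that for the primary analyses "multivariate logistic regression is adopted to calculate adjusted odds ratios (ORs) and 95% confidence interval (95% CI) for short-term outcomes". It continues: "Cox proportional hazard regression analysis is used to generate adjusted hazard ratio (HR) and corresponding 95% CI for long-term outcomes". It does not say which of the two classes 12-month TLR belongs to, and it names neither the covariates nor the estimator. The same section puts the noninferiority margin at 10 percentage points on the absolute difference.

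The Primary outcome section defines the endpoint as "Target lesion revascularization (TLR) of the target lesion(s) assessed at 12 months after the intervention", counted "when the primary patency is lost". Under Secondary outcomes, "the loss of primary patency is defined as target lesion(s) is determined to be > 50% stenosis or TLR/TLR needed in follow up". Every TLR is therefore a patency loss, but not every patency loss is a TLR. In Follow-up and outcomes of interest, the condition for reintervention begins "If the restenosis is more than 50% and the patient" and goes on to require worse symptoms as well.

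The Sample size calculation uses 9-month patency of 89.1% (CBE) and 82.2% (CSE) and a 15% dropout rate, and concludes: "It was calculated that 53 lesions per group are needed for a total of 106 lesions". No TLR rate is given anywhere. The Discussion credits an earlier study of the CBE stent with satisfactory 9-month results, "including a low rate of TLR for the treatment of stenotic and occlusive lesions of the iliac arteries", without a figure.

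**The concern.** A multivariable logistic or Cox model needs enough events to support its coefficients. A model with arm, age, sex and number of legs (the randomisation factors) has four coefficients besides any intercept. At 13 events that is about 3 events per coefficient.

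Two things follow. First, maximum-likelihood odds ratios are then biased away from 1, and their large-sample intervals are unreliable. Second, if one arm has no TLR, the estimated log odds ratio runs off to infinity and has no usable Wald interval; a Cox hazard ratio does the same. Under the plan's own rates the empty arm is more likely to be the CBE arm, that is, when the tested stent does best. At stake are the adjusted effect estimate for the primary endpoint and the freedom to pick a replacement method after an empty cell has been seen. The TASC and occlusion/stenosis subgroups divide the same few events again.

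**Working it through.** **1. The plan's own figure.** Noninferiority on a risk difference, unpooled variance, one-sided 5%, 80% power:

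n = (1.645 + 0.842)² × (0.822×0.178 + 0.891×0.109) / (0.10 + 0.891 − 0.822)² = 6.183 × 0.2434 / 0.0286 = 52.7, so 53 per group.

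This is the size before dropout; 53/0.85 = 62.4, so 63 after it. That discrepancy is a separate matter. Here it means only that both denominators need showing: 53 (all analysed) and 53 × 0.85 ≈ 45 (evaluable after dropout).

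**2. Expected patency losses** at 10.9% and 17.8%:
- 45 per arm: 45×0.109 + 45×0.178 = 4.9 + 8.0 = 12.9
- 53 per arm: 5.8 + 9.4 = 15.2

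These are means. With 45 per arm the 95% range of the count is 7 to 20, and the chance of more than 13 is 42%.

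**3. From losses to TLR.** The documents give no TLR rate, so assume that a fraction f of losses leads to TLR. The chance of an empty arm is (1 − f·p)ⁿ. For example, with f = 0.5 in the CBE arm: (1 − 0.0545)⁴⁵ = 0.080.

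| f (assumed) | Expected TLRs, 45/arm | No CBE event | No CSE event | Expected TLRs, 53/arm | No CBE event |
|---|---|---|---|---|---|
| 1 | 12.9 | 0.6% | 0.02% | 15.2 | 0.2% |
| 0.5 | 6.5 | 8.0% | 1.5% | 7.6 | 5.1% |
| 0.33 | 4.3 | 19% | 6.6% | 5.0 | 14% |
| 0.25 | 3.2 | 29% | 13% | 3.8 | 23% |

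With f = 0.5 and 45 per arm, the chance that either arm is empty is 1 − (1 − 0.080)(1 − 0.015) = 9.4%.

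**4. Bias when the estimate is finite.** The true log odds ratio at the patency-loss rates is ln(0.109/0.891) − ln(0.178/0.822) = −0.57. A simulation with assumed covariates gave a mean of −0.69 by maximum likelihood and −0.61 by Firth's method, with root mean squared errors of 0.71 and 0.63. The maximum-likelihood bias is thus 0.12 on the log scale. Its size depends on the assumed covariates. A repeat of 4,000 trials (45 per arm; 20% female, 40% bilateral and standardised age, all unrelated to outcome; trials with a non-finite treatment estimate left out for maximum likelihood) gave −0.62 and −0.57.

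**5. The noninferiority test with an empty cell.** Newcombe 95% intervals for CBE minus CSE, 45 per arm, no CBE event. For 0 versus 0, each Wilson upper limit is 3.84/(45 + 3.84) = 7.9%, so the upper limit of the difference is +7.9 points. For 0 versus 1, 3 and 8 events it is +5.9, +2.3 and −6.2 points. All lie below the 10-point margin.

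**The case against.** The strongest reply is that noninferiority is judged on an absolute difference, so an infinite odds ratio does not stop the trial from reaching its conclusion. Step 5 confirms this, and the section also lists Fisher's exact test for categorical data. That part of the reply stands. A reader might infer that the primary analysis collapses in the trials most favourable to the CBE stent; this is true of the adjusted odds or hazard ratio only. It remains that the only models named for the primary analyses give an odds ratio or a hazard ratio, and Fisher's test gives no interval to set against the margin.

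Three further limits also stand:
- A reader might take 13 as a maximum. It is an expected count for completers at 9-month rates. Modified intention-to-treat with multiple imputation points towards 15, chance can take it to about 20, and the endpoint is at 12 months.
- A reader might cite simulated failure rates of about 8% at the patency-loss rates and 39% at half of them (five assumed covariates, 45 per arm). Those count trials in which any coefficient is non-finite, mostly nuisance covariates. The treatment estimate itself fails in about 1% and 9%.
- A reader might infer that TLRs will be far fewer than patency losses. The definitions point to fewer, but how many fewer is not documented.

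It can also be said that estimator, covariates and fallback belong in an SAP that is not shown, and that the article names neither maximum likelihood nor Wald intervals. That is fair, and an SAP that already specifies a sparse-data method would close the point. The concern here is not the missing detail. It is that the model class the article names, fitted in the usual way, does not suit the number of events its own figures imply.

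**Conclusion.** The point holds in limited form. The plan's planning rates imply about 13 (45 per arm) to 15 (53 per arm) expected patency losses, and TLR is a subset of these. At the patency-loss rates an ordinary adjusted odds ratio is biased away from 1, by roughly 0.05 to 0.12 on the log scale in the two simulations, which rest on assumed covariates. That is small beside the sampling error, but it can be avoided. With 45 evaluable lesions per arm, an empty CBE arm occurs in 0.6% of trials at the documented rates and in 8% if half of the losses lead to TLR; figures above 0.6% depend on an assumed TLR fraction. If 12-month TLR is instead analysed by Cox regression, an empty arm causes the same failure. The documents do not support the stronger conclusion that the noninferiority decision is at risk. This is worth correcting before analysis, but it does not invalidate the design.

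**What to change.** For TLR and other rare endpoints, pre-specify Firth-penalised logistic regression (or Firth-penalised Cox, if 12-month TLR is treated as long-term) with profile-likelihood intervals, adjusted only for the randomisation factors: age as a continuous variable, sex and number of legs. State separately that noninferiority is judged on a risk-difference interval that stays valid with zero cells, for example Newcombe or Miettinen-Nurminen, against the 10-point margin; Firth's odds ratio does not supply this. Report the two subgroup comparisons descriptively, as event counts by arm.

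The cost is wording. No extra patients are needed, and standard R packages do the work. The downside is slight shrinkage of the estimates.

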**Methods:**

This trial is a prospective, single-center, parallel, noninferiority, randomized controlled trial. A total of 106 patients will be enrolled and these patients will be randomized to either the CBE stent group or the CSE stent group. The primary end point of the study is the occurrence of target lesion revascularization (TLR) at 12 months after the intervention.

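### The 10-point risk-difference margin is never compared with a confidence limit: the primary analyses name only odds and hazard ratios, and two failed analyses would satisfy the success rule as worded

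*Protocol article*

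**What the plan says.** The margin is absolute in both places where the protocol article gives it. Sample size calculation: "the predetermined noninferiority margin on risk difference scale (δ) is set as 10% between treatment groups". Statistical analysis: "The noninferiority margin was set at 10 percentage points for the absolute difference between groups".

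The primary endpoint is binary at a fixed time. Abstract, Methods: "The primary end point of the study is the occurrence of target lesion revascularization (TLR) at 12 months after the intervention".

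For the primary analyses, the Statistical analysis section names two models. The first is "multivariate logistic regression is adopted to calculate adjusted odds ratios (ORs) and 95% confidence interval (95% CI) for short-term outcomes". The second is "Cox proportional hazard regression analysis is used to generate adjusted hazard ratio (HR) and corresponding 95% CI for long-term outcomes". The main analysis set is a modified intention-to-treat set (randomized and then treated), with a per-protocol analysis as sensitivity.

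The same section holds two statements on the decision:
- "If the standard of noninferiority was reached, the primary and secondary outcomes were subsequently tested for superiority"
- "Noninferiority will be considered proven if conclusions drawn from the intention-to-treat and per protocol analyses are consistent"

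No estimate of, or interval for, a difference in risks is named. The margin is not converted to an odds or hazard ratio, and the standard that opens the way to superiority testing is not defined.

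**The concern.** A noninferiority conclusion needs three things on one scale: an estimate, a confidence limit and a margin. Here the margin is a difference and the named estimates are ratios. A ratio can be set against a 10-point difference only by assuming a control risk, and the article gives no 12-month TLR risk for either stent.

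The only explicit rule for declaring success then asks for agreement between two analyses, not for each to exclude the margin. It also refers to intention-to-treat, although the set defined in that section is the modified one.

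Noninferiority is the design of this trial, so the gap falls on its confirmatory conclusion.

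**Working it through.** **1. The plan's own figure.** Inputs from Sample size calculation: primary patency 82.2% (CSE) and 89.1% (CBE) at 9 months, margin 10 points, type I error 0.05 with sidedness not stated, power 80%. With the margin on the risk-difference scale and unpooled variance:

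n = (z₁₋α + z₀.₈₀)² × [0.822×0.178 + 0.891×0.109] / (0.10 + 0.069)²

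- One-sided 0.05: (1.645 + 0.842)² × 0.2434 / 0.02856 = 52.7, so 53 per group.
- One-sided 0.025: (1.960 + 0.842)² × 0.2434 / 0.02856 = 66.9, so 67 per group.

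The stated 53 is therefore a risk-difference calculation at one-sided 0.05, before any dropout allowance. Design and margin share a scale; the named analysis does not. The dropout allowance is a separate matter, not pursued here.

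**2. The margin on the ratio scales.** For control risk p, OR = [(p+0.10)/(0.90−p)] / [p/(1−p)]. Under proportional hazards, HR = ln(0.90−p)/ln(1−p).

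| Control (CSE) risk | Source | OR | HR |
|---|---|---|---|
| 17.8% | 1 − 82.2%, 9-month patency loss | 1.78 | 1.66 |
| 10% | assumed | 2.25 | 2.12 |
| 5% | assumed | 3.35 | 3.17 |
| 3% | assumed | 4.83 | 4.57 |

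The reverse also fails. If OR 1.78 were fixed as the margin and the control risk were 5%, the odds would be 1.78 × 0.05/0.95 = 0.0937 and the risk 0.0937/1.0937 = 8.6%. The margin would then be 3.6 points, not 10.

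**3. Can the scale change the verdict?** Illustration with assumed counts, 53 per group, unadjusted Wald 95% intervals.

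*6 CBE against 9 CSE events.*
- Risk difference: 0.113 − 0.170 = −5.7 points; SE = √(0.113×0.887/53 + 0.170×0.830/53) = 0.0675; interval −18.9 to +7.6. The upper limit is below 10, so noninferiority is met.
- Odds ratio: (6/47)/(9/44) = 0.62; SE of the log = √(1/6 + 1/47 + 1/9 + 1/44) = 0.567; interval 0.21 to 1.90. The upper limit is above 1.78, so noninferiority is not met.

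*3 against 3 events.*
- Risk difference: 0, upper limit +8.8 points. Met.
- Odds ratio: 1.00, interval 0.19 to 5.19. The upper limit exceeds every converted odds ratio in the table. Not met.

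**4. The success rule.** There are four possible pairs of results: both analyses exclude the margin, only one does (two ways), or neither does. The two analyses agree in the first and the last. Read literally, the rule counts the last as proof. Only the first should count.

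**5. What the confidence level costs.** Power at the planning rates is Φ[0.169/SE − z₁₋α], with SE = √(0.2434/n) and 45 ≈ 53 × 0.85.

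| Evaluable lesions per group | 90% CI (one-sided 0.05) | 95% CI (one-sided 0.025) |
|---|---|---|
| 53 | 80% | 70% |
| 45 | 74% | 63% |

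**The case against.** The best defence is that the section reports categorical data as numbers and rates and calls the margin an absolute difference. A reader would then naturally judge noninferiority on the difference in rates, with the adjusted ratios reported alongside, and a statistical analysis plan could supply the interval. Much of this is fair. A risk difference can be derived from the stated logistic model or from the raw proportions, so a reader who inferred that the trial cannot decide noninferiority at all would go too far. Nor do the documents support an inference that a ratio threshold would be chosen after seeing the data, since an unseen plan could fix one beforehand. What remains is that the article is not silent: it names ratios as the output of the primary analyses and says nothing of a difference.

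The agreement rule was probably meant as noninferiority shown in both sets, and intention-to-treat there is probably shorthand for the modified set. The documents do not show that anyone intends to claim success after two failures. The sentence is still the only explicit success rule, and it does not say what was probably meant.

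It may also be said that a binary endpoint at 12 months clearly belongs to the logistic model. That is likely, though the section does not assign it, and either model leaves the scale problem.

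A reader might further infer that the adjusted model would be overfitted. The article names no covariates and gives no TLR rate, so that does not follow.

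**Conclusion.** The point holds as wrong wording in the stated text, and it should be corrected because it governs the confirmatory conclusion. The margin and the named primary estimates are on different scales, no confidence limit is compared with the margin, and the success rule does not separate two successes from two failures.

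The size of the mismatch depends on the control risk: the 10 points correspond to odds ratios from 1.78 to 4.83 as that risk falls from 17.8% to 3%. Only 17.8% comes from the protocol, and it is 9-month loss of patency, not 12-month TLR; the other risks are assumed. The opposite verdicts in the illustration rest on assumed counts and unadjusted Wald intervals. They show that the choice of scale can decide the result, not how often it would.

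**What to change.** 1. **Primary estimate.** Name the CBE-minus-CSE difference in 12-month TLR risk. Obtain it by marginal standardisation of the logistic model already planned, or from Kaplan-Meier 12-month risks. Cluster standard errors by patient where a patient contributes more than one lesion; the sample size is counted in lesions and bilateral disease is allowed. Keep odds and hazard ratios as supportive.

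2. **Decision rule.** Replace the agreement sentence with: *Noninferiority is shown only if the upper limit of the two-sided 95% confidence interval for this difference is below 10 percentage points in both the modified intention-to-treat and the per-protocol sets. Superiority is then tested by whether that limit is below 0.* The 95% level is the one the Statistical analysis section already uses.

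3. **Power.** State the level in the sample size section and restate the power to match.

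**Cost.** Analysis wording and a few lines of code, with no new data. The real price is power: at the planning rates the 95% interval gives about 70% with 53 evaluable lesions per group and 63% with 45, against 80% and 74% with a 90% interval. Keeping 80% power at the 95% level would need 67 evaluable lesions per group. If the sponsor prefers the 90% interval, which is what 53 per group reflects, the text should say so and justify it.

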### Allocation and implementation of interventions

Prior to the endovascular intervention, patients will be enrolled, and informed consent will be obtained from all participants by surgeons. The included patients were randomly allocated at a 1:1 ratio to the CBE stenting group or the CSE stenting group using Statistical Analysis System (SAS, version 9.4) by a biostatistician within sex and 5-year age groups in blocks of ten, and stratification was performed by numbers of treatable legs. For patients who required intervention in bilateral iliac arteries, randomization was performed according to the treated arteries. The sealed, opaque, consecutively numbered envelopes were used to keep the allocation code for each participant, which will be kept unopened by an independent research assistant. The nurse research coordinator in the operating room will prepare the envelopes and inform the surgeon of the allocation results before intervention. Both nurse research coordinators and biostatisticians were not involved in the perioperative management of patients. The outcome assessors and data analysts will be blinded to the interventions.

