### Details of intervention

The included patients will receive the same perioperative management, including antiplatelet drugs, statin usage, and blood controls. Both common femoral arteries and sometimes brachial artery will be used for access. Whether to adopt percutaneous or cutdown access route will be determined by the surgeons. After obtaining arterial access, 0.5 mg/kg of unfractionated heparin will be administered. A fluor opaque ruler will be used to record the location and extent of the lesion. Both intraluminal and subintimal recanalization of iliac lesions will be allowed. After the successful passage of the guidewire, the target lesion will be predilated with downsized balloon in CBE group, and with equal-sized balloon in CSE group. During actual intervention, the allocated choice of covered stents may be modified according to intraoperative findings, for instance, the length of lesions did not match the stents. Multiple stents are required when needed and multiple stent edges should overlap by at least 10 mm. Furthermore, additional bare metal stents can be added in both groups, according the discretion of surgeons. Post-dilation balloon will be performed within the stented segment, with less than 10% oversizing. Final angiography will be performed after the intervention in both groups, with the same angles and magnifications as the baseline angiography.

Postoperative management include a dual antiplatelet regimen for 3 months, involving 100 mg of aspirin once a day plus 75 mg of clopidogrel once a day. Clopidogrel is not required if a participant is taking warfarin; other direct thrombin inhibitors, factor Xa inhibitors, or low molecular weight heparin will be used according to the physician’s recommendation. Anticoagulant therapy will be discontinued when other surgical procedures are needed, and then, the participant will resume anticoagulant therapy as soon as possible after the surgery. Drug side effects will be checked and monitored at outpatient visit or telephone follow-up. According to the comprehensive surgeon’s recommendation, drug therapy will be discontinued. Clinical follow-up will be planned at 1, 6, 12, 24, and 36 months to evaluate clinical outcomes.

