### CBE and CSE stent

The CBE stent used in our trial is BARD® LIFESTREAM™ Covered Stent, a permanent stent used to maintain patency of the common or external iliac artery. The stent is a balloon-expandable stent with expanded polytetrafluoroethylene (ePTFE) encapsulated between two layers (inner and outer). The implant is pre-mounted on an over-the-wire balloon catheter that acts as the delivery system. The configurations of BARD® LIFESTREAM™ covered stent offered 16, 26, 37, 38, and 58 mm in length and 5 to 12 mm in diameter. The stents can be overlapped if the target lesion exceeds the longest available length of stent.

GORE® VIABAHN™ self-expandable covered stent is the only CSE stent adopted in our trial; it consists of two main components: an intravascular covered stent and a catheter-based delivery system. The stent consists of a self-expanding nickel-titanium alloy stent combined with an ePTFE intracavity coating, which is offered in lengths of 25, 50, and 100 mm and in diameters of 5 to 11 and 12 mm in the configurations.

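### The set called per-protocol is defined by the stent received, although stents may be switched for anatomy, and the non-inferiority rule asks only that two analyses agree

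*Protocol article*

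**What the plan says.** All on this point comes from the protocol article.

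- **Primary set** (Statistical analysis): a "modified intention-to-treat analysis, which includes all subjects undergo randomization and subsequent interventions".
- **Second set** (same section): "Sensitivity analyses of primary and secondary endpoints are performed in the per-protocol population, based on the treatment actually received".
- **Margin** (same section): "The noninferiority margin was set at 10 percentage points for the absolute difference between groups".
- **Decision rule** (same section): "Noninferiority will be considered proven if conclusions drawn from the intention-to-treat and per protocol analyses are consistent".
- **Switching** (Details of intervention): "the allocated choice of covered stents may be modified according to intraoperative findings, for instance, the length of lesions did not match the stents".
- **Knowledge of allocation** (Allocation and implementation of interventions): the research nurse is to "inform the surgeon of the allocation results before intervention".
- **Device lengths** (CBE and CSE stent): the CBE stent is "offered 16, 26, 37, 38, and 58 mm in length and 5 to 12 mm in diameter"; the CSE stent is "offered in lengths of 25, 50, and 100 mm". The same section allows CBE stents to be overlapped in lesions longer than the longest stent.

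**The concern.** There are two separate faults.

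**The second analysis set.** A per-protocol set normally keeps patients in their randomised arm and leaves out those who departed from the allocated treatment. Grouping by treatment received is something else: a lesion allocated to CBE but given CSE would count as CSE. The switch is made by a surgeon who knows the allocation, for anatomical reasons. If those reasons also predict failure, and switching is unequal between arms, the comparison is confounded by the anatomy that drove the switch. In a non-inferiority trial this analysis is there to check that switching has not diluted the randomised comparison, so its own validity matters.

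**The decision rule.** It asks that two conclusions be consistent. It does not say that each must show non-inferiority, and it mentions neither the confidence limit nor the margin. Two analyses that both fail are consistent. The rule also refers to intention-to-treat, whereas the set defined a few lines earlier is modified intention-to-treat.

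Nothing here questions whether switching should be allowed. The point is how switched lesions are analysed.

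**Working it through.** The plan gives no figure for switching, for the share of long lesions or for the effect of length, so there is no plan figure to reproduce. Everything below except the 53 lesions per group and the 10-point margin is assumed.

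**1. Size of the confounding, no true stent difference.** Assume 30% long lesions failing at 30% and the rest failing at 10% with either stent. Each arm of 53 then has 53 × 0.30 = 15.9 long and 37.1 other lesions. Let a share *s* of long CBE lesions receive CSE, with no switching the other way.

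- CBE as received: (37.1 × 0.10 + 15.9(1 − s) × 0.30) / (37.1 + 15.9(1 − s))
- CSE as received: (37.1 × 0.10 + 15.9(1 + s) × 0.30) / (37.1 + 15.9(1 + s))

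| s | CBE as received | CSE as received | Spurious gap |
|---|---|---|---|
| 10% | 8.00/51.41 = 15.6% | 8.96/54.59 = 16.4% | 0.8 points |
| 33% | 6.89/47.7 = 14.4% | 10.07/58.3 = 17.3% | 2.8 points |

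If the same shares of long lesions moved from CSE to CBE instead, the gap would be the same size against CBE. If equal shares moved both ways, each group would again hold 15.9 long lesions and the gap would be zero.

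**2. What excluding switched lesions achieves.** At s = 33%, dropping the switched lesions leaves CBE at 6.89/47.7 = 14.4% and CSE at (3.71 + 4.77)/53 = 8.48/53 = 16.0%, a gap of about 1.6 points. Exclusion removes part of the bias and leaves selection, which is why adjustment is also needed.

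**3. Simulation under different assumptions.** 53 per arm; one-sided 0.05 Wald limit against 10 points (the plan does not state sidedness); 100,000 trials per scenario; 40% long lesions; CSE patency 75% in long and 87% in other lesions; 0%, 25% or 50% of long CBE lesions switched to CSE.

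| | 0% | 25% | 50% |
|---|---|---|---|
| *Stents equal: mean difference in favour of CBE, points* | | | |
| As randomised | 0.0 | 0.0 | 0.0 |
| As treated | 0.0 | 1.4 | 3.0 |
| Switched lesions excluded | 0.0 | 0.8 | 1.8 |
| *CBE truly 10 points worse: trials meeting the criterion* | | | |
| As randomised alone shows non-inferiority | 5.6% | 7.0% | 8.8% |
| As treated alone shows non-inferiority | 5.6% | 7.7% | 11.2% |
| Rule read literally: the two agree | 100% | 95% | 91% |
| of which both fail | 94% | 90% | 86% |
| Both must exclude the margin (as treated as second set) | 5.6% | 5.0% | 5.6% |
| Both must exclude the margin (switched excluded as second set) | 5.6% | 5.5% | 6.2% |

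With length not prognostic and CBE truly 10 points worse, as-treated grouping was unbiased (−10.0 points), while the randomised comparison was diluted to −9.0 and −8.0 points at 25% and 50% switching.

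**The case against.** A reader might infer that the trial's conclusion rests on a comparison biased towards CBE, because 58 mm against 100 mm would push long lesions from CBE to CSE. The documents do not support that. Overlapping CBE stents is expressly provided for, so a lesion beyond 58 mm need not be switched. Length mismatch is only an example, and no direction or frequency is given. Modified intention-to-treat stays primary. If both analyses must pass, a bias in the second cannot by itself produce a claim of non-inferiority: in the simulation the joint requirement held the false-positive rate at 5.0% to 5.6% even with as-treated grouping.

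A reader might also infer that the investigators would declare non-inferiority after two failed analyses. That is unlikely. The same paragraph sets a 10-point margin and makes superiority testing conditional on reaching the non-inferiority standard, so the probable intent is that both analyses meet the margin. This makes the second fault chiefly one of wording. It still needs correction, because this is the only sentence that says when non-inferiority is proven.

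Two further replies carry some weight. The definition could mean a set selected by whether the allocated stent was received; the text does not say that switched lesions change arm. And the article already plans adjusted models, whose covariates may be listed in an analysis plan not shown. Neither removes the point: the definition as printed reads most naturally as as-treated, and it is a stated rule, not an omission.

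**Conclusion.** The point holds in a limited form. The set labelled per-protocol is worded as as-treated while anatomy-driven switching is permitted. That confounds the second analysis if lesion length is prognostic and switching is unequal between arms. Neither condition is established by the documents, and overlap may keep switching rare. Under the stated assumptions, the illustrative bias is 0.8 to 2.8 points for 10% to 33% switching (1.4 to 3.0 in the simulation for 25% to 50%). This is not negligible against a 10-point margin, but it affects a supporting analysis.

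The decision rule is defective as written, whatever those assumptions: agreement between two failures satisfies it. Once both analyses are required to exclude the margin, the choice of second set changes the simulated false-positive rate little. Correcting the rule therefore protects the conclusion most; correcting the set makes the second analysis what its name says.

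**What to change.** 1. **Analysis set.** Define the per-protocol set as lesions that received the allocated stent type without major deviation, analysed in the randomised arm and adjusted for lesion length or TASC class. Label any analysis by stent received as as-treated and exploratory.
2. **Decision rule.** Replace the consistency sentence with: non-inferiority is concluded only if the upper confidence limit for the CBE minus CSE risk difference in target lesion revascularization is below 10 percentage points in both the modified intention-to-treat and the per-protocol analysis.

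The cost is two sentences and a slightly smaller per-protocol set, since switched lesions drop out of it (5.3 of 53 CBE lesions in the 33% illustration, 1.6 of 53 at 10%). No further patients are needed.
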